## Abstract

**Background:**

The Namaste Care program is a person-centered intervention that has been shown to improve the quality of life of people with dementia and to alleviate caregiver burden. However, its application in China remains underexplored. Given China’s unique sociocultural norms, cultural adaptation is essential to ensure feasibility, acceptability, and contextual fit.

**Objective:**

The primary objective is to culturally adapt the Namaste Care Home Program to the Chinese community context. The secondary objective is to evaluate the feasibility and acceptability of the adapted program (qualitative analysis), and to explore its preliminary effects (quantitative analysis) on quality of life and related outcomes for people with dementia and their family caregivers.

**Methods:**

A 3-stage, 11-step mixed methods design is used in this study. The process includes a baseline stage for community assessment and stakeholder consultations, a formulation stage for adapting the intervention and training materials, and an execution and evaluation stage in which trained family caregivers deliver the intervention. A 1-group, pretest-posttest design will be used, with quantitative assessments at baseline (T0), immediately after intervention (T1), and at the 3-month follow-up (T2), complemented by qualitative process evaluations.

**Results:**

The study was approved in April 2025 (2025-NZY-4‐01) and registered on April 18, 2025 (ChiCTR2500101042). Recruitment occurred from January to April 2025, enrolling 15 caregiver–people with dementia dyads. As of April 2025, baseline data collection is complete, and analysis is ongoing. Primary results are expected in mid-2026.

**Conclusions:**

The cultural adaptation of the Namaste Care Home Program is a critical step toward advancing person-centered, home-based dementia care in China. Findings will provide evidence on feasibility and cultural appropriateness and will inform the design of future large-scale trials to test effectiveness in cross-cultural settings.

## Introduction

Dementia affects over 55 million individuals globally and is projected to triple by 2050 [1,2], with more than 60% of people with dementia living in low- and middle-income countries (LMICs). China alone accounts for approximately 20% of global cases, posing a major public health challenge [3]. Dementia leads to cognitive decline, behavioral and psychological symptoms of dementia, progressive dependence, and reduced quality of life (QoL) for people with dementia and their families [4-6].

In China, caregiving is predominantly family based under the influence of filial piety, with over 96% of care provided by family members who often lack formal training [7,8]. Consequently, more than 80% of caregivers experience anxiety, depression, and high strain [9,10]. Institutional care exists but is costly and often viewed as temporary, reinforcing reliance on home-based care [11].

Nonpharmacological interventions such as cognitive stimulation therapy [12] and reminiscence therapy [13] are widely used, yet benefits concentrate in the early to middle stages; their reliance on cognitive abilities limits feasibility for advanced dementia and may not align well with China’s family-care context [6,14]. In contrast, Namaste Care requires minimal verbal ability, can be delivered by trained family caregivers at home, is a relatively low resource, and targets comfort and behavioral and psychological symptoms of dementia through multisensory engagement—priorities for moderate-to-advanced dementia in China’s predominantly home-based care [6,12-16].

Developed in Western settings, Namaste Care emphasizes emotional- and sensory-focused engagement and has shown promise in improving QoL among people with moderate-to-advanced dementia [15,16]. However, the existing evidence is primarily from Western contexts, and there is no culturally adapted Namaste Care model that has been evaluated in China [9,17]; thus, the applicability, feasibility, and effectiveness under China’s family-based caregiving norms remain uncertain. Accordingly, this protocol outlines the cultural adaptation of Namaste Care for China and a mixed methods feasibility evaluation to inform subsequent multicenter testing.

The primary objective is to culturally adapt the Namaste Care Home Program (NCHP) for the Chinese community context. The secondary objectives are to: (1) evaluate feasibility (eg, recruitment, retention, and adherence) and acceptability from family caregivers’ perspective (qualitative analysis); (2) explore preliminary effects on QoL among people with dementia (quantitative analysis); and (3) explore preliminary effects on caregivers’ outcomes, including QoL, caregiving burden, caregiving abilities, attitudes toward dementia, and positive aspects of caregiving (quantitative analysis).

## Methods

### Study Design

This protocol uses a 3-stage mixed methods design guided by the 11-step adaptation framework proposed by Escoffery [18]. This structured approach ensures a systematic process, from community needs assessment to intervention implementation and evaluation, as illustrated in Figure 1.

**Figure 1. F1:**
[figure not shown]
Framework for evidence-based adaptation of interventions. EBIs: evidence-based interventions; NCHP: Namaste Care Home Program.

#### Stage 1: Baseline Stage (Steps 1-5)

##### Step 1: Assess Community

We selected Lianyungang, Jiangsu (Chaoyang Community Health Service Center) based on facility readiness, participant engagement, and transport accessibility, aligned with the local priority of aging in place [19] (ethics approval: 2025-NZY-4‐01; refer to the Ethical Considerations section). The detailed steps are shown in Figure 2.

**Figure 2. F2:**
[figure not shown]
NCHP adaptation and implementation framework. EBI: evidence-based intervention; NCI: Namaste Care International; NCHP: Namaste Care Home Program.

##### Steps 2-3: Understand and Choose the Evidence-Based Intervention

A comprehensive review of nonpharmacological interventions for moderate-to-advanced dementia informed evidence-based intervention (EBI) selection under resource constraints in LMICs [1]. We selected Namaste Care for its sensory- and emotion-focused components, home deliverability by family caregivers, and stage appropriateness. In addition to these practical considerations, its philosophy, embodied in the respectful *namaste* greeting, aligns with the Chinese cultural values, such as compassionate caregiving and filial piety. A brief comparative rationale versus cognitive stimulation therapy or reminiscence therapy is provided in the Introduction section.

##### Step 4: Consult with Experts

We consulted [name] (founder of Namaste Care) and [name] (Honorary Chair, Namaste Care International) through webinars and email exchanges to draw on global adaptation experience and to delineate core components, identify adaptable elements, and gather guidance on community implementation [20].

##### Step 5: Consult with Stakeholders

We conducted structured meetings with caregivers, community directors, and nurses to map care challenges, knowledge gaps, and preferred delivery formats, thereby generating an initial context, mechanism, and outcome specification for adaptation. We anticipate engaging approximately 12 to 18 stakeholders (eg, 8‐12 family caregivers, 2‐3 community directors, and 2‐3 nurses), sampling will continue until information power is adequate for decision-making.

### Stage 2: Formulation Stage (Steps 6-8)

#### Step 6: Decide What Needs Adaptation

The team will identify China-specific modifications while preserving the NCHP’s core objectives, principles, and theoretical foundations. Drawing on initial stakeholder feedback and a review of implementations in other regions, we will specify changes to setting, materials, and training so that activities are practical for home use and can be integrated into daily routines. Community nurses, caregivers, and family members will be convened to finalize these adaptations, ensuring alignment with Chinese caregiving values and practice norms. Outputs will include a China-adapted specification that distinguishes core from adaptable elements.

#### Step 7: Adapt the Original Program

We will complete the conceptual translation and simplify and standardize procedures to support delivery by community nurses and family caregivers. Daily activities will be tailored to the capabilities of people with dementia, and brief group sessions will be scheduled twice weekly to encourage regular participation (Textbox 1).

Textbox 1.Adapted Namaste Care Home Program (NCHP) delivery schedule (daily routines and twice-weekly group activities).
**Daily activities**

**Morning sessions**
Preparatory work Food and drink preparation: seasonal availability, individual preference, swallowing condition Personal care items: NCHP bags (eg, hand cream, face cream) Room setup: soft lighting, soothing aromatherapy, relaxing musicLife care and activities Morning greetings Facial care: facial cleansing, applying face cream, and rubbing face Hand care: hand cleaning, hand cream massage Traditional Chinese medicine health care: swallowing exercises, finger exercises, meridian tapping, head soothing, finger combing hair, tooth tappingNutritional supplements Snacks: lotus root powder, sesame paste Intermittent hydration: water, Chinese floral teas, soy milk
**Noon sessions**
Abdominal massage (Fairy kneading manipulation)Nap for 20‐30 minutes
**Afternoon sessions**
Activities Creative activities: paper cutting, painting, colorful doodling, reminiscence therapy, doll therapy Games: tossing game, card game Traditional Chinese cultural activities: listening to opera, crosstalk, and storytelling Outdoor activities: low-angle sunbathing (3‐5 PM) and walkingNutritional supplements Food: fruit platter or fruit puree Intermittent hydration: water, milk (avoid drinks that affect sleep)
**Evening sessions**
Life careFoot care: warm water foot soak, foot massageSleep care: Chinese herbal aromatherapy for sleep aid (Acorus calamus, Albizia Flower, etc), applying body lotionFinish work Touching the back of the hand and patting the back Praising the people with dementia for their cooperation throughout the day Document the people with dementia’s activity preferences and complete the NCHP checklist
**Group activities (twice weekly)**
Competitive activities: marble grabbing and ring toss gameCultural and social gatherings: Red Song parties and tea partiesCreative activities: horticultural therapy, flower arrangement, DIY handicrafts, and creating a family calendarFestival Activities: making rice dumplings and sachets, making mooncakes, paper cutting, and making dumplings

The adapted package will retain the program’s core principles while addressing 5 elements (Figure 3): (1) applicability to daily life (affordable, familiar items, eg, Pechoin SOD emulsion; Tong Ren Tang vitamin E lotion and selected traditional Chinese medicine–informed practices such as head soothing and finger combing; food choices that meet nutritional and swallowing needs); (2) group activities that foster social and cultural engagement (eg, paper cutting, Red-Song gatherings, and tea parties); (3) blending with fun through enjoyable and functional games (eg, tossing and card games) to stimulate cognition and mobility; (4) family involvement via tasks that promote participation and strengthen bonds (eg, family calendars and joint activities); and (5) traditional festival participation to increase relevance and feasibility.

**Figure 3. F3:**
[figure not shown]
Five elements of the adapted Namaste Care Home Program (NCHP) are depicted here.

The adapted materials will be reviewed by [name] to ensure fidelity to the core principles. To assess acceptability and practicality, we will conduct 2 to 3 focus group (6‐8 participants each) discussions with community nurses, caregivers, and family members [20], guided by the Bowen feasibility framework and acceptability theory [21,22]; interview guides (Table S1 in Multimedia Appendix 1) will be used to structure data collection [23]. Additionally, 10 to 15 semistructured caregiver interviews will be conducted, and data collection will continue until adequate information power and evidence of theme saturation are reached. Semistructured interviews will also elicit feedback on the activity checklist and item list to finalize personalized NCHP checklists and NCHP bags, and caregivers will review the NCHP manual.

#### Step 8: Select and Train Caregivers

We will use criterion sampling [21] to recruit eligible dyads. Eligibility criteria for people with dementia include (1) age 60 years or older; (2) moderate-to-severe dementia as determined by the Mini-Mental State Examination [22], clinical symptoms, and caregiver report, confirmed by a trained evaluator; (3) medically stable; and (4) community-dwelling (noninstitutionalized). Caregiver eligibility criteria include (1) age 18 years or older; (2) provision of continuous, 24-hour in-home care for at least 3 months; and (3) ability to communicate effectively.

We will recruit a feasibility sample of 10 to 15 dyads to assess recruitment, retention, adherence, and acceptability rather than to test hypotheses [23]. Previous feasibility studies of Namaste Care and similar interventions have used comparable sample sizes [24], and Bowen et al [25] recommend using small sample sizes for exploratory feasibility objectives. Eighteen dyads were screened, and 3 were excluded, 4 dyads completed a 2-week pilot test, and all 15 dyads then proceeded to the 3-month intervention. (See Figure 4 for participant flow).

**Figure 4. F4:**
[figure not shown]
CONSORT-style participant flow for the 1-group feasibility protocol.

### Pilot Sample-Size Justification

This feasibility study prioritizes estimation precision over hypothesis testing. Therefore, we adopt a precision-based rationale for 10 to 15 dyads. For feasibility proportions (eg, 3-month retention and weekly adherence), a sample of 15 dyads yields an approximate 95% CI half-width of about +22 or –22 percentage points when the true rate is around 75% (and about +27 or –27 percentage points for n=10), which is sufficient to judge performance against feasibility thresholds. For continuous outcomes, a sample of 10 to 15 dyads provides approximately 24% to 19% relative precision for the SD (RSE(σ)≈√[1/(2(n−1))]), which is adequate to inform sample-size calculations for a subsequent trial. Regarding safety, if no adverse events (AEs) are observed, the “rule of three” places the upper 95% confidence bound on per-dyad AE risk at approximately 3/n (ie, no more than 20% for n=15), providing an acceptable early-phase safety screen. Taken together and consistent with previous feasibility studies of Namaste Care and related dementia interventions, a sample of 10 to 15 dyads is sufficient and appropriate to estimate key feasibility metrics and guide the design of a larger study.

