#### Feasibility Metrics

Feasibility benchmarks will be based on prior work [30] and will include the following: (1) NCHP application frequency (goal: ≥3 days per week, with ≥4 hours on at least 1 of those days); (2) retention over 3 months (goal: ≥75%, consistent with dementia-care feasibility studies [31]); and (3) incidence of AEs (goal: 0%; potential AEs include skin breakdown and falls). Although we aim for 0%, any AE will be closely monitored and addressed per protocol [32]. These thresholds will guide go, modify, or stop decisions for a subsequent trial: ≥75% for both retention and adherence=proceed; 60%‐74% for both=proceed with modifications; <60% for either metric=redesign, conditional on safety (no serious adverse events [SAEs] and all AEs appropriately managed).

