## Results

Recruitment was conducted from January to April 2025 and yielded 15 caregiver–people with dementia dyads (n=30). Caregivers had a mean age of 65.7 (SD 11.7) years; 60% (9/15) were women, 66.7% (10/15) were married, and 73.3% (11/15) were retired or not working. People with dementia had a mean age of 83.5 (SD 6.8) years; 60% (9/15) were men, 66.7% (10/15) were in the moderate stage of dementia, 33.3% (5/15) were in the late stage, and 46.7% (7/15) were married, while 53.3% (8/15) were widowed. Recruitment is now closed, baseline assessments are complete, and data analysis is ongoing. Detailed participant characteristics are presented in Tables3  4.

**Table 3. T3:** Characteristics of caregivers (n=15).

Characteristics	Participants, n (%)	
Age (years)		
45‐59	4 (26.7)	
60‐74	6 (40)	
≥75	5 (33.3)	
Gender		
Men	6 (40)	
Women	9 (60)	
Nonbinary	0 (0)	
Marital status		
Married	10 (66.7)	
Widowed	2 (13.3)	
Divorced	3 (20)	
Employment status		
Working	4 (26.7)	
Not working or retired	11 (73.3)	

**Table 4. T4:** Characteristics of people with dementia (n=15).

Characteristics	Participants, n (%)	
Age (years)		
75‐79	4 (26.7)	
80‐84	6 (40)	
≥85	5 (33.3)	
Gender		
Men	9 (60)	
Women	6 (40)	
Nonbinary	0 (0)	
Marital status		
Married	7 (46.7)	
Widowed	8 (53.3)	
Stage of dementia category		
Moderate	10 (66.7)	
Late	5 (33.3)	

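### The quoted precision of ±22 points (n=15) or ±27 points (n=10) does not support the claim that it is enough to judge against feasibility cut-offs only 15 points apart

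*Protocol article*

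**What the plan says.** Step 8 sets the target: "We will recruit a feasibility sample of 10 to 15 dyads". The Results section reports that recruitment, now closed, "yielded 15 caregiver–people with dementia dyads (n=30" individuals), so n=15 is the realised size.

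Pilot Sample-Size Justification rests the sample on precision. For the feasibility proportions, which include retention and adherence, it states: "a sample of 15 dyads yields an approximate 95% CI half-width of about +22 or –22 percentage points". That figure is for an assumed rate near 75%; with 10 dyads the stated half-width rises to roughly 27 points. It then says of this precision: "which is sufficient to judge performance against feasibility thresholds".

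Feasibility Metrics defines the thresholds. The top tier is "≥75% for both retention and adherence=proceed"; 60% to 74% on both means going ahead with modifications; below 60% on either means redesign, all subject to a safety condition. On their use: "These thresholds will guide go, modify, or stop decisions for a subsequent trial". The article does not say whether the rule is read against the observed rate or a confidence limit, and it gives no probabilities of reaching each decision.

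**The concern.** The adequacy claim is an inference from interval width to a decision rule, so the width has to be compared with the spacing of the rule. The middle zone is 15 points wide, whereas the interval is about 44 points wide at n=15 (2 × 22) and wider at n=10. An interval that size, centred anywhere near the cut-offs, reaches into all three zones.

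This sentence is the rationale for the sample size as far as the feasibility proportions go, and those proportions drive the progression decision. The Discussion also says retention and adherence estimates will feed the next trial's sample-size calculations. A reader who accepts the sentence would credit a proceed or redesign result with a degree of support that 10 to 15 dyads rarely give.

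**Working it through.** **Inputs.** True rate 75%, n=15 and n=10, 95% confidence (Pilot Sample-Size Justification); cut-offs 75% and 60% (Feasibility Metrics). Assumptions: z=1.96, and each metric is a count of dyads out of n.

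**Step 1: reproduce the plan's figures.** Half-width = 1.96 × √[p(1−p)/n].
- n=15: 1.96 × √(0.75 × 0.25/15) = 1.96 × 0.1118 = 0.219, or 21.9 points.
- n=10: 1.96 × √(0.75 × 0.25/10) = 1.96 × 0.1369 = 0.268, or 26.8 points.

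Both stated figures reproduce.

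**Step 2: set them against the cut-offs.** The gap is 75 − 60 = 15 points. The interval at 75% is about 53% to 97% for n=15, and about 48% to 100% (capped) for n=10. Each reaches below 60% and above 75%.

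**Step 3: exact intervals for possible results.** Clopper-Pearson limits for x of n are the 2.5% quantile of Beta(x, n−x+1) and the 97.5% quantile of Beta(x+1, n−x). At n=15, proceed means 12 or more, modify 9 to 11, redesign 8 or fewer.

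| Result | Observed | Exact 95% CI | Zone by observed rate |
|---|---|---|---|
| 4/15 | 26.7% | 7.8–55.1% | redesign |
| 7/15 | 46.7% | 21.3–73.4% | redesign |
| 8/15 | 53.3% | 26.6–78.7% | redesign |
| 9/15 | 60.0% | 32.3–83.7% | modify |
| 11/15 | 73.3% | 44.9–92.2% | modify |
| 12/15 | 80.0% | 51.9–95.7% | proceed |
| 13/15 | 86.7% | 59.5–98.3% | proceed |
| 14/15 | 93.3% | 68.1–99.8% | proceed |
| 15/15 | 100% | 78.2–100% | proceed |

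Every count from 8 to 13 has an interval containing both 60% and 75%. Only 15/15 lies wholly at or above 75%, and only 4/15 or fewer lies wholly below 60%. At n=10, 10/10 has a lower limit of 0.025^(1/10) = 69.2%, so no result establishes 75% or more.

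Wilson intervals change little. At n=15, 13/15 then just excludes 60% (lower limit 62.1%) and 5/15 falls below it (upper limit 58.3%). At n=10, 10/10 still has a lower limit of only 72.2%.

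**Step 4: how the rule behaves on observed rates.** Binomial probabilities for one metric at n=15:

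| True rate | Proceed | Modify | Redesign |
|---|---|---|---|
| 90% | 94% | 6% | 0% |
| 85% | 82% | 17% | 0.4% |
| 75% | 46% | 48% | 6% |
| 60% | 9% | 52% | 39% |
| 50% | 2% | 29% | 70% |

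Rows may not sum to 100% because of rounding.

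**The case against.** The best defence is that this is a feasibility study, that Step 8 disclaims hypothesis testing, and that Feasibility Metrics says only that the thresholds guide decisions. Nothing there requires a confidence limit to clear a cut-off. Read on observed rates, the rule behaves tolerably: two-zone errors are uncommon even at the cut-offs (6% redesign at a true 75%, 9% proceed at a true 60%), and a programme truly at 90% or 50% is usually placed correctly. That stands, and it is why the rule itself can stay. It does not rescue the sufficiency clause, which argues from interval width and fails on that ground.

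Several stronger readings are tempting but unsupported:
- *That the sample can make no judgement at all.* Extreme results settle the zone, 14/15 rules out redesign, and 7/15 or fewer rules out proceed.
- *That a 46% chance of proceeding at a true 75% shows n=15 to be inadequate.* A rule on observed rates passes about half the time at its own cut-off for any sample size, so that row cannot be read alone. The 60% row also sits on a boundary.
- *That the article's arithmetic is wrong.* It is not, and the figures are labelled approximate.
- *That decisions will be reported without intervals.* The article does not say so.

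**Conclusion.** The sufficiency clause claims a property that the design does not have, while the numbers it rests on are correct. The half-width exceeds the 15-point gap at both ends of the planned range, and at n=15 the middle run of results (8 to 13 of 15) leaves both cut-offs inside the exact interval. This is an error of interpretation that one sentence can repair. It does not invalidate the study, the sample size or the progression rule, and the article also cites SD precision, a safety bound and precedent for its size.

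The calculations assume dyads as the counting unit. That fits retention directly. Weekly adherence might instead be summarised over dyad-weeks, in which case its interval would depend on within-dyad correlation, which the article does not give. The operating characteristics are for one metric. The rule needs both, and the joint probability depends on how strongly retention and adherence go together, which is also not stated.

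**What to change.** - Replace the sufficiency clause in Pilot Sample-Size Justification with a statement that 10 to 15 dyads estimate the feasibility proportions only coarsely and cannot reliably separate 75% from 60% except at extreme results.
- In Feasibility Metrics, state that the three-tier rule is applied to observed rates as indicative guidance.
- Report retention and adherence with exact or Wilson 95% intervals beside the decision.
- If operating characteristics are given, show them across a range of true rates, as in the second table above, and not only at the cut-offs.

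This costs a few sentences and, optionally, one small table. No further dyads are needed, and neither the rule nor the planned analysis changes. The downside is a less favourable account of what the sample can show. Recruitment is closed, but the wording can still be corrected before results are reported.
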